**Significance:**

Our expected result is that the developed model of severe influenza can be more accurate and have a lower misdiagnosis rate than traditional clinical assessment. The pre-specified AUC was 0.18 (95% CI: 0.14-0.22), with an expected 32% reduction in misdiagnosis. The model’s performance was consistent across patients in older adults, underlying disease, and resource-poor areas. The added value of the study is that it is effective in improving early recognition of severe influenza.

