Data: data were obtained from 87 hospitals in Jiangsu Province, China. The data features of interest were clinical information, laboratory test results, and demographic information.Stages: 5 research phases with model building, internal validation, comparative study, randomised trial, and prospective real-world validation.Collaboration: the aim of the model is to assist clinicians in accurately identifying patients with severe influenza.

We hypothesize that this model will significantly improve AUC (*Δ* > 0.15) compared to physician-only assessments, reduce misdiagnosis rates by ≥30%, and maintain robustness across hospitals with varying resource levels. By addressing both algorithmic and human factors, this research seeks to establish a scalable solution for mitigating influenza-related mortality, particularly in resource-constrained settings.

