#### Calculation rationale

2.5.1

The sample size was determined based on the primary outcome (AUC comparison between model-assisted and clinician-only diagnoses) using a two-group superiority design. Key parameters were derived from prior studies on AI diagnostic tools (31, 32):

Expected effect size: ΔAUC = 0.15 (clinically meaningful improvement).

Type I error (*α*): 0.05 (two-tailed).

Power (1-*β*): 0.95.

Attrition rate: 20% adjustment for patient dropout or incomplete data.

The minimum sample size for AUC comparison was calculated using the following formula (33):

$$n=\frac{{\left(Z_{1-\alpha /2}+Z_{1-\beta }\right)}^{2}\times [\mathrm{AU}C_{1}(1-\mathrm{AU}C_{1})+\mathrm{AU}C_{2}(1-\mathrm{AU}C_{2})]}{{\left(\mathrm{AU}C_{1}-\mathrm{AU}C_{2}\right)}^{2}}$$

Where:

$\mathrm{AU}C_{1}$
 (model-assisted): 0.85 (34).

$\mathrm{AU}C_{2}$
 (clinician-only): 0.70 (null hypothesis).

$Z_{1-\alpha /2}$
= 1.96, 
$Z_{1-\beta }$
= 1.645.

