#### Justification

2.5.4

The patient sample size was determined through a power analysis to ensure ≥80% statistical power for detecting a clinically meaningful improvement (ΔAUC more than 0.15) in diagnostic accuracy, aligning with FDA guidelines for validating AI-driven medical devices (36).

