#### Subgroup analyses

2.8.3

Subgroup analyses will evaluate the model’s performance heterogeneity across predefined categories: patient-level factors (age [infants, children, adults, older adults], comorbidities, and vaccination status), clinician-level factors (experience [resident, attending, chief] and hospital resource tier [urban vs. rural]), and geographic variation (northern vs. southern Jiangsu Province). To mitigate bias, statistical adjustments include Bonferroni correction for multiple comparisons (adjusted *α* = 0.05 / number of subgroups) and multivariable logistic regression controlling for confounders such as seasonal trends, baseline viral load, and treatment delays. These analyses aim to identify subgroups where the model excels or underperforms, ensuring tailored clinical deployment and validating robustness across diverse healthcare settings.

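### Robustness across hospital resource levels is to be validated by Bonferroni-corrected subgroup tests without a margin, and such tests can show a difference but not that accuracy is maintained

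*Protocol article*

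**What the plan says.** The Introduction lists three hypotheses. Two carry a number: an AUC gain above 0.15 and a misdiagnosis reduction of at least 30%. The third is that the model will "maintain robustness across hospitals with varying resource levels", and it has no numerical criterion.

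Section 2.8.3 compares performance by age, comorbidity, vaccination, clinician experience, hospital tier and region. The adjustments it names are "Bonferroni correction for multiple comparisons" at 0.05 divided by the number of subgroups, and a multivariable regression for confounders. It gives two aims: to find subgroups where the model does well or badly, and "ensuring tailored clinical deployment and validating robustness across diverse healthcare settings". Section 2.4.3 lists the same factors and the same correction.

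The Abstract, under Significance, says that the model's "performance was consistent across patients in older adults, underlying disease, and resource-poor areas". The paragraph opens as a statement of expected results.

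The sample size is built for the overall comparison only. Section 2.5.1 has "Expected effect size: ΔAUC = 0.15 (clinically meaningful improvement", "Type I error (*α*): 0.05 (two-tailed") and "Power (1-*β*): 0.95". Section 2.5.4 restates the power as "to ensure ≥80% statistical power for detecting a clinically meaningful improvement". Section 2.5.3 sets the total at 348 patients, retrospective and prospective together. No power or precision is given for any subgroup.

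**The concern.** Finding a subgroup that differs and showing that subgroups perform alike are opposite inferential tasks. A test of no difference, corrected for multiplicity, suits the first: Bonferroni limits false claims of heterogeneity. For the second, the costly error is to miss a real loss. There the correction works the wrong way, because each added subgroup lowers the alpha and makes a loss harder to detect.

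The hypothesis concerns hospitals with fewer resources, which is where the authors want to deploy the tool. If accuracy were materially lower in rural hospitals and the planned test did not flag it, nothing in section 2.8.3 would stop robustness from being reported as validated.

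**Working it through.** **The 348.** Section 2.5.2 goes from 145 to 174 per group (145 × 1.2), and 2 × 174 = 348. The printed formula with its stated inputs gives (1.96 + 1.645)² × (0.85 × 0.15 + 0.70 × 0.30) / 0.15² = 194.9 per group, not 145. That is a separate matter. Here 348 is taken as the number available.

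**Number of tests.** Age 4 levels, comorbidities 2, vaccination 2, experience 3, tier 2, region 2: six factors, fifteen levels. The article does not say which count divides alpha, so both are shown. Critical values: 1.960 at 0.05, 2.638 at 0.05/6, 2.935 at 0.05/15.

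**Formula.** Hanley-McNeil variance for a tier with n₁ severe and n₀ non-severe patients:

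Var(A) = [A(1−A) + (n₁−1)(Q₁−A²) + (n₀−1)(Q₂−A²)] / (n₁n₀), with Q₁ = A/(2−A) and Q₂ = 2A²/(1+A).

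SE of the difference = √(Var₁ + Var₂). Power of the two-sided z-test ≈ Φ(d/SE − z); miss rate = 1 − power.

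**Base case.** Assumed, because the article gives neither: equal tiers and 20% severe. Each tier then has 174 patients, 34.8 of them severe.

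- A = 0.85 (the model-assisted AUC of section 2.5.1): variance 0.00181.
- A = 0.75: variance 0.00259.
- SE = √(0.00181 + 0.00259) = 0.066; d/SE = 0.10/0.066 ≈ 1.51.
- Miss rate: 67% at 0.05, 87% at 0.05/6, 92% at 0.05/15.

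**Range at 348 patients** (severe share 10-50%, smaller-tier share 20-50%, the smaller tier having the lower AUC):

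| AUC in the two tiers | Miss rate at 0.05/6 | Miss rate at 0.05/15 |
|---|---|---|
| 0.85 vs 0.75 | 70-96% | 79-98% |
| 0.85 vs 0.70 | 34-92% | 46-96% |

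With the article's own variance, A(1−A)/n, which ignores the severe share, the 0.10 loss at an equal split is still missed 61% of the time at 0.05/6 and 72% at 0.05/15.

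**Robustness read as an equal gain in both tiers.** Four cells of 348/4 = 87 patients, 20% severe. The gain is 0.15 in one tier (0.85 vs 0.70) and nil in the other (0.70 vs 0.70). SE = √(0.00365 + 3 × 0.00573) = 0.144. The interaction is missed 82% of the time at 0.05 and 97% at 0.05/15.

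**Larger record sets.** Section 2.1.1 requires at least 100 confirmed cases per hospital: 87 × 100 = 8,700, and the 20% internal validation share is 1,740. Base case, 0.10 loss, at 0.05/15: missed 33% of the time at 1,740 and about 0% at 8,700. A 0.15 loss at 1,740 is missed 2% of the time. With 10% severe or a 20% smaller tier, a 0.10 loss at 1,740 is still missed more often than not at 0.05/15 (69% and 64%).

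**The case against.** The strongest reply is that the harmful rule is nowhere written. No sentence says that a non-significant test will be read as consistency. Section 2.8.3 says it evaluates heterogeneity and looks for subgroups where the model under-performs, and a corrected difference test is conventional for that. This stands. A reader might infer a decision rule from the closing phrase of the section, but the text does not state one. What remains is that the section offers these analyses as the validation of robustness and gives no other route to that claim.

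Second, an analysis plan not shown here may hold a margin, and interpretation rules for subgroups are often left to it. That is fair as to the missing margin alone. The point here is that the article itself fixes a method, with its alpha, and assigns it a claim that the method cannot support.

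Third, the denominator is unclear. Section 2.5.3 says 348 in total, but sections 2.3.1 and 2.3.5 describe records from all 87 hospitals. The miss rates therefore depend on which set is analysed. This also stands.

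Fourth, the hypothesis names hospital resource levels only. Applying it to age groups, comorbidities or regions goes beyond it. The Abstract's consistency sentence is in the past tense, but it sits among expected results and need not be read as a finding already made.

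**Conclusion.** The mismatch between method and claim holds whatever the sample size: a corrected difference test with no margin cannot establish that accuracy is maintained across hospital tiers. Its practical size depends on the denominator. At 348 patients and under the assumed shares, a 0.10 loss of AUC between tiers would usually be missed (70-96% at 0.05/6, 79-98% at 0.05/15). Hospital clustering and the planned 20% attrition would tend to raise these figures.

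Two stronger readings are not supported. One is that any large loss would usually be missed: for a 0.15 loss with equal tiers and half the patients severe, the miss rate is 34% at 0.05/6 and 46% at 0.05/15, and with the larger record sets most of the power problem goes away. The other is that the authors have committed themselves to reading non-significance as consistency; the article leaves that open. The severe share, the tier split and the number of tests are all assumptions.

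**What to change.** In section 2.8.3:

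- Keep Bonferroni only for claims that a subgroup differs.
- For the robustness hypothesis, report the AUC difference between tiers, urban minus rural with the direction fixed in advance, with an uncorrected 95% CI. Claim robustness only if that CI excludes a loss larger than a margin the sponsor states in advance. Otherwise report that robustness was not established.
- State which patients or records enter this analysis.
- Report the other subgroup differences with CIs as descriptive.
- Reword the validation phrase in section 2.8.3 and the consistency sentence in the Abstract to match.

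The cost is wording and a few intervals from data already planned; no extra patients are needed. The downside is that at 348 patients, 20% severe and an equal split, the CI is about ±1.96 × 0.066 = ±0.13, so robustness will probably be reported as not established. That is a more accurate statement of what 348 patients can show.

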#### Missing data handling

2.8.4

To address missing data, variables with more than 20% missing values (such as incomplete vaccination records) will be excluded to maintain analytical reliability. For remaining gaps, multiple imputation via chained equations (MICE package in R) will generate 10 imputed datasets for continuous variables, preserving statistical power under missing-at-random assumptions. Categorical variables with less than 10% missingness will undergo mode imputation, replacing missing entries with the most frequent category, while those exceeding this threshold will be excluded to avoid biased estimations. This protocol balances data completeness with methodological rigor, minimizing potential distortions in model performance evaluation.

#### Sensitivity analyses

2.8.5

To evaluate the robustness of findings, sensitivity analyses will include complete case analysis (comparing results with and without imputation) and model stability assessments (quantifying AUC variation across imputed datasets). These analyses ensure conclusions are not unduly influenced by missing data assumptions. For computational workflows, R (v4.3.1), Python (v3.10), and Stata (v18) will be utilized, integrating specialized packages for imputation (MICE), AUC calculation (pROC), and regression modeling. Reporting will adhere to the Transparent Reporting of a multivariable prediction model for Individual Prognosis or Diagnosis (TRIPOD) guidelines for transparent validation of predictive models, ensuring methodological transparency, reproducibility, and alignment with international standards for AI-driven diagnostic research.

## Ethics and dissemination

3

This study received ethical approval from the Ethics Committee of the Affiliated Hospital of Yangzhou University (Approval No. 2024-10-02). Annual renewals of ethical approval will be submitted to ensure ongoing compliance with evolving regulatory and ethical standards. Informed consent was obtained from all participants: patients or their legal guardians (for minors or incapacitated adults) provided written consent for anonymized data collection and analysis, while clinicians signed agreements acknowledging their roles in diagnosis and model interaction, with the explicit right to withdraw at any time. To safeguard privacy, all patient identifiers were replaced with unique study codes, and anonymized data were stored on the OSF platform (osf.io/ayj75), accessible only to authorized researchers via two-factor authentication. These measures align with international data protection standards and China’s Data Security Law, ensuring ethical integrity and participant confidentiality throughout the study.

### Risk mitigation

3.1

To ensure patient safety and research integrity, clinicians retain full authority to override model recommendations if conflicting with clinical judgment, while an independent adjudication panel reviews all severe outcomes to confirm diagnostic accuracy. Emergency unblinding is permitted only when critical safety concerns necessitate full diagnostic transparency, with such instances documented and reviewed by ethics committees.

### Dissemination plan

3.2

For broader dissemination, results will be shared across all 87 participating hospitals via workshops and a bilingual Clinical Decision Support Guide, with plans to integrate model outputs into EHR systems post-regulatory approval. Findings will be submitted to peer-reviewed journals and presented at international forums, complemented by public health bulletins highlighting implications for high-risk populations.

### Data sharing policy

3.3

Data collected during the study will be stored under the supervision of the Ethics Committee of Yangzhou University Hospital. The China Clinical Research Registry advocates that data from clinical trials should be de-identified and then proactively disclosed, which is conducive to improving research transparency. However, we prefer to comply with the General Data Protection Regulation (GDPR) and China’s Data Security Law. This approach is conducive to gaining public trust and greatly protects the privacy of clinical trial participants. If a researcher is interested in the data, he or she should obtain ethical approval from the researcher’s institution and write a satisfactory and necessary research protocol. Once this has been done, the investigator can apply by email to the corresponding author. It is important to know that access involving sensitive human data must be subject to the jurisdiction and approval of the ethics committee. and Lidström et al. also advocate for the protection of patient data security (37).
